# Makes FLASH the difference between the intervention group and the treatment-as-usual group in an evaluation study of a structured education and treatment programme for flash glucose monitoring devices in people with diabetes on intensive insulin therapy: study protocol for a randomised controlled trial

**DOI:** 10.1186/s13063-018-2479-9

**Published:** 2018-02-05

**Keywords:** Diabetes, Flash glucose monitoring, Patient education and treatment programme, Psychoeducation, Self-management, Patient-reported outcome

## Abstract

**Background:**

People with diabetes on intensive insulin therapy need sufficient glycaemic control to prevent the onset or progression of diabetic complications. The burden of multiple daily blood glucose self-testing can be lessened by novel diabetes technology like flash glucose monitoring systems which provide more information compared to self-monitoring of blood glucose. Despite this delivered additional information studies are showing no significant effect on HbA_1c_ reduction, but a reduced time spent in a hypoglycaemic glucose range. We assume that users of these devices need additional education and training to integrate the delivered information into treatment decisions. Therefore, FLASH, an education and treatment programme, was developed. The programme evaluation follows herein.

**Methods/design:**

Patients are recruited through 40 diabetes outpatient study centres located across Germany. They will be randomly assigned to participate in the education and treatment programme (intervention group) or to obtain treatment as usual (control group). All patients have to give blood samples and to answer a bench of questionnaires during baseline assessment, at the end of the intervention, and 6 months after the end of the intervention. Physicians will be asked to declare some additional clinical data (such as details of the diabetes therapy) for every patient at every one of the three assessment points.

**Discussion:**

This study is conducted as a randomised controlled trial to test the hypothesis that the newly developed education and treatment programme combined with the use of a flash glucose monitoring device (intervention group) is superior to reduce HbA_1c_ compared to the use of flash glucose monitoring alone (control group). The first results will be expected in 2018.

**Trial registration:**

ClinicalTrials.gov, ID: NCT03175315. Registered on 2 May 2017.

**Electronic supplementary material:**

The online version of this article (10.1186/s13063-018-2479-9) contains supplementary material, which is available to authorized users.

## Background

Diabetic patients on intensive insulin therapy with multiple daily injections or continuous, subcutaneous insulin infusion need to achieve sufficient glycaemic control to prevent the onset or progression of diabetic complications [1, 2], while at the same time avoiding the risk of severe hypoglycaemia.

Successful intensive insulin treatment requires close self-monitoring of blood glucose (SMBG). Measurement of blood glucose is especially important before main meals because the prandial insulin dose will vary with blood glucose level, planned carbohydrate consumption, and other factors (e.g. exercise, alcohol consumption). The multiple daily skin pricks and the need to carry a blood glucose meter, test strips, lancets, and blood glucose log books can be very trying, and patients often get frustrated [3]. However, novel technologies, such as flash glucose monitoring, can provide relief.

Flash glucose monitoring provides continuous measurement of interstitial glucose levels via a glucose sensor placed in the subcutaneous tissue of the upper arm [4, 5]. This sensor can be left at the insertion site for 14 days, and the interstitial glucose level obtained whenever necessary by scanning with a reader or smartphone using near-field technology. In addition to the current glucose level, the reader or smartphone will also display arrows indicating the long-term trend in interstitial glucose level (slightly/strongly increasing, slightly/strongly decreasing, or stable) and the course of the glucose level over the last 8 h.

Flash glucose monitoring has several benefits over SMBG. Multiple daily skin pricks can be avoided. Glucose levels can be painlessly measured any number of times by scanning with a reader and, moreover, the results are automatically stored for 90 days. Software can display glucose patterns and provide information on additional parameters, such as time spent in predefined glycaemic ranges (e.g. hypoglycaemic or hyperglycaemic range), median and mean glucose values, or an estimation of the current glycated haemoglobin level (HbA_1c_), based on the previous collected and stored interstitial glucose values.

This new technology also has some downsides. Users need to be educated on how to integrate all the additional information (e.g. trend arrows, previous course of glucose) into treatment decisions. Problematic glucose patterns requiring treatment adjustments can be easily identified, but only if the user has the necessary knowledge and skills.

Two previous studies [1, 2] have shown that flash glucose monitoring has no significant effect on HbA_1c_, although it does reduce time spent in the hypoglycaemic glucose range. We hypothesise that education on how to make optimal use of flash glucose monitoring devices would improve outcomes. We therefore developed a programme, FLASH, to support these patients. We are planning a randomised controlled trial (RCT) to determine the effect of FLASH on HbA_1c_ as well as on secondary outcomes (i.e. time spent in different glucose ranges, patient-reported outcomes, and device satisfaction). The purpose of this paper is to present the research protocol of the planned study.

## Methods/design

### Study setting

The study is designed as a multicentre study. A total of 40 diabetes outpatient treatment centres located across Germany have been invited to recruit eligible patients for the study. A study centre is defined as a medical practice run by a diabetologist and where diabetes nurses or certificated diabetes educators (CDE) are also available. The course instructors for FLASH will be CDE. Prior to the study, the course instructors will undergo an intensive 8-h training in the study protocol and the education and treatment programme. This programme will be conducted by the research team. Course instructors will be provided with a written curriculum and audiovisual teaching material, along with detailed descriptions of each slide. Additionally, trainers from the coordination research institute (Research Institute of Diabetes Mergentheim: FIDAM) will visit each participating medical centre, and course instructors can then resolve any doubts about the conduct of the programme. In these visits FIDAM employees will confirm that the slides of the FLASH will operate and could be displayed in each medical praxis and that the course instructor knows how to conduct the programme, fully understands the content of the programme, can clarify any likely questions, and knows how to upload the therapy data from the flash glucose monitoring reader to Diasend®. During the course of study, all study centres will have a hotline to FIDAM for support. FIDAM will communicate with all participating study centres via newsletters where every new development can be presented promptly and reliably. Conversely, the coordinating centre will be available for the responsible personnel in the study centres for the entire duration of the study. In addition to conducting the education and treatment programme, the physicians at the study centres will be responsible for the therapy of their patients during and after the study.

### Study design

This multicentre RCT will enroll diabetic patients on intensive insulin therapy who are using flash glucose monitoring. The patients will be randomised into one of two groups: an intervention group and a control group. Both groups will receive the flash monitoring device and technical instructions on its use; the intervention group will receive, in addition, FLASH training.

### Sample size calculation

A total of 86 patients per group will be necessary to detect a mean difference of 0.3% and a standard deviation of 0.7% in HbA_1c_ reduction between the two treatment groups (Cohen’s *d* = 0.43), with an alpha error = 0.05 and beta = 0.2 (power = 0.8). Given an expected non-evaluable rate of 20%, a total of 216 participants will be needed, with 108 patients in each group.

### Recruitment and randomisation

All participating study centres will identify eligible patients interested in participating in the study. The eligible patients will be offered an appointment to get to know the facts of the study, to clarify doubts, and to give signed informed consent. Because no education programme for patients using flash glucose monitoring devices is available, medical centres and patients are showing great interest in participating in this study. However, despite the great interest it is possible that the required sample size will not be achieved. In this case there are more medical centres available which can be contacted for patient recruitment. Patient recruitment will be stopped after 216 patients are enrolled.

Baseline assessment will take place over two visits. At the first visit, blood will be collected, baseline questionnaires will be completed, patients will be provided with the flash glucose monitoring device and receive technical instructions, and the sensor will be implanted. Blinded FIDAM staff will review all baseline assessments to confirm that the enrolled patients meet all the eligibility criteria. Then, randomisation of patients will be done centrally at FIDAM using SYSTAT version 12, with random assignment at the level of the study centre. The results will be sent to the respective study centres in sealed envelopes that will be opened only at the second baseline visit. At this second visit, 2 weeks after the first visit, patients will be informed of the group assignment. Glucose-level data from the reader will be uploaded via Diasend® (see below: ‘Assessments’).

### Inclusion and exclusion criteria

#### Inclusion criteria

Patients of either sex will be eligible for inclusion in the study if they fulfil the following conditions:Age 16–75 yearsOn intensified insulin therapy/insulin pump therapyPrevious participation in at least one structured diabetes education programmeHbA_1c_ in the range of 7.5–14%Reduction of HbA_1c_ as the therapeutic goalAble to understand, speak, and write GermanWilling to provide informed consent (if necessary, informed consent of the parents)Have an indication for using a flash glucose monitoring system

Indication for a flash glucose monitoring system will be decided by the treating physician. The decision will be based on the following: (1) frequent unexplicable glucose levels and need for multiple daily measurement of blood glucose; (2) severe hypoglycaemic events, especially during the night; hypoglycaemic unawareness; and (3) undue patient anxiety about the use of the lancet, but otherwise good compliance with the device.

#### Exclusion criteria

Patients will be excluded if they have any of the following:Diabetes duration < 1 yearType 2 diabetes not on insulin, or on non-intensified insulin therapySevere organic disease preventing regular participation in the training coursePregnancySevere cognitive impairmentCurrent treatment of a psychiatric disorderRenal disease requiring dialysis

The treating physician will confirm that each patient satisfies the inclusion and exclusion criteria by checking the health records or by clinical assessment. Once included in the study, patients may still be excluded from the analysis if they decide to leave the study at any point for any reason, or if they miss any one treatment appointment or one of the three assessment points.

The REPLACE and IMPACT studies [1, 2] were not able to show significant improvement in glycaemic control with flash glucose monitoring vs. SMBG. Assuming that education might be able to improve the efficacy of flash glucose monitoring, exclusion of patients with previous flash glucose monitoring system use is not necessary (since the device alone does not seem to be efficacious in improving the HbA_1c_). The main objective of this study is not to prove the efficacy of flash glucose monitoring systems, but rather to evaluate the efficacy of the FLASH education and treatment programme. However, if there are substantial differences between the control and intervention groups in previous flash glucose monitoring system use, adjustment will be made during the analysis for experience of using previous flash glucose monitoring systems.

### Content, structure and intervention of FLASH

FLASH is a structured education and treatment programme that will be delivered in a group setting, with each group comprising three to eight patients in the age range 16–75 years. This wide age range was selected so that study centres could include as many eligible patients as possible. Previous experience has shown that it is difficult to recruit homogeneous age groups. Having patients of widely differing ages is not necessarily a disadvantage, since younger people with diabetes can learn from the experiences of older ones and vice versa. If important differences are observed between the different age groups, adjustment for these factors will be made during analysis of data.

FLASH aims to empower patients by providing information and teaching strategies for better self-management of diabetes. FLASH participants are encouraged to be actively involved in their treatment: they formulate their own therapy-related goals, learn to recognise patterns in their glucose levels and to identify trends, and also to use this information for optimising daily therapy decisions. During FLASH, participants are also invited to share their experiences with flash glucose monitoring with other group members. The ultimate objective is to teach patients to live active and normal lives through efficient use of flash glucose monitoring.

FLASH uses different modern educational techniques. The guiding principle is self-management, especially self-monitoring, self-assessment, and enhancing self-treatment. Participants are provided with written material and worksheets and are encouraged to test the contents of each lesson on their own and to then discuss their experiences in the group setting. They are introduced to computer-based data analysis software and learn how to use it for optimising their own therapy. Additionally, patients define what they personally hope to achieve by attending the FLASH programme. Course instructors are provided with core content about the interpretation of flash glucose monitoring results and also optional content in slides on a secondary level if more detailed information is needed on a certain topic (e.g. exercising or hypoglycaemia).

The FLASH programme takes place over 6 weeks. It consists of four sessions, lasting 90 min each. There is a 1-week interval between sessions 1 and 2, and 2-week intervals between sessions 2 and 3 and sessions 3 and 4. These intervals give patients time to practise the newly learned techniques in their daily lives. Table 1 provides an overview of FLASH.

**Table 1 Tab1:** Overview of FLASH: aims, content, and didactics

Session	Aim	Key content	Special didactical feature
1 First week	Information about, and motivation for, using of flash glucose monitoring	Principles of flash glucose monitoring	Clarification of features of the device
		Understanding trend arrows	Personal motivation
2 Second week	Recognition of glucose pattern	Analysing glucose values and trends	Introduction to the 6 modules on AGP: steps 1–2: understanding the AGP.
			Intensive discussion about glucose value documentation and computer-based data analysis software
3 Fourth week	Therapy adjustment based on pattern recognition and AGP	Using data to recognise glucose patterns and to adjust the therapy	The 6 modules (continued): modules 3–6: interpreting the AGP, and therapy adjustment.
			Intensive discussion and amplification by personal examples
4 Sixth week	Check of the adjustment of the therapy	Dealing with barriers	Reinforcement of lessons learned
			Preparing methods for long-term management

*AGP* ambulatory glucose profile

The *first session* focusses on the function of the flash glucose monitoring system and on interpretation of the trend arrows. The emphasis will be on teaching patients how to make therapy adjustments based on the information derived from the trend arrows.

The *second session* introduces patients to ambulatory glucose profile (AGP) monitoring (modules 1–2 of the six modules on AGP). Patients will learn to systematically analyse their glucose profiles and to organise the information from the flash glucose monitoring system.

The *third session* focusses on pattern recognition (modules 3–6). Participants will learn how to interpret the AGP and use it for therapy adjustment. Simple case studies will be used to teach participants to recognise typical patterns. Possible causes for these patterns and the appropriate therapy adjustments will be discussed.

The *fourth* and final session focusses on the changes in the AGP due to therapy adjustments. Individual cases on therapy adjustment during FLASH will also be discussed. Participants will be given an opportunity to share practical tips on how to handle minor day-to-day problems.

FLASH was developed in consultation with a group of experts (diabetologists and diabetes educators with special experience in flash glucose monitoring) according to German and international guidelines. The contents and lessons were discussed with the experts over the course of 1 year and were refined based on patients’ experiences with flash glucose monitoring. FLASH has a written curriculum to be followed by educators and study material for patients like worksheets used during courses as well as tasks for the time at home in which the patients will have to test the content of the preceding course.

Figure 1 shows how the patients were assigned to the two treatment arms.

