### Planned data analysis

Continuous data over all three time points will be summarised using descriptive statistics. Differences across the time points will be calculated for each group. The distributions of these differences will be compared using analysis of variance (ANOVA) for repeated measurements, with the FLASH group as the independent variable. If significant baseline differences are seen, the respective baseline values will be used as covariates.

Sometimes the questionnaire data may be skewed and may not fulfil the criteria for interval data. Assuming that at least rank-order data are available from the questionnaires, we will use either non-parametric tests for the evaluation of questionnaires and glucose data, or perform a transformation of the scores and glucose parameters into van der Waerden scores before applying parametric tests. Based on the data distribution and the scale of measurement, appropriate statistical methods will be selected. In the case of categorical data determined over several time points, we will use logistic regression analysis with adjustment for baseline values.

Statistical testing will be conducted at a significance level of *α* = 0.05. All analyses will be performed using SYSTAT version 12.0. For the intention-to-treat analysis missing data will be substituted by the last-observation-carried-forward method.

All data will be treated as confidential and be stored at FIDAM, the study coordination centre, for 10 years. Only FIDAM personnel will have access to the data during the study. FIDAM will monitor the flow of participants through each stage of the trial, and finally will be able to publish it.

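### FLASH is taught in groups in one arm only, but the sample size and the ANOVA assume independent patients, so error control and the stated 80% power depend on a course correlation near zero

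*Protocol article*

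**What the plan says.** Under Content, structure and intervention of FLASH, the programme is "delivered in a group setting, with each group comprising three to eight patients". The same section has participants exchange and discuss their experience with the device, and Study setting puts each course in the hands of a certificated diabetes educator. According to Study design, controls receive the device and technical instructions; no course is described for them.

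Under Sample size calculation, the article states: "A total of 86 patients per group will be necessary to detect a mean difference of 0.3% and a standard deviation of 0.7" percentage points in HbA1c reduction. The only inflation is for attrition: "Given an expected non-evaluable rate of 20%, a total of 216 participants will be needed, with 108 patients in each group".

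Planned data analysis: "The distributions of these differences will be compared using analysis of variance (ANOVA) for repeated measurements, with the FLASH group as the independent variable". In context, that variable is the treatment arm. The other adjustments mentioned in the article are conditional: baseline values in that section, previous device use under Exclusion criteria, and age under the content of FLASH. No term for course, educator or centre is named.

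Recruitment and randomisation says that patients are randomised centrally, but also that assignment is made at study-centre level. It does not say whether this means allocation within each centre or allocation of whole centres.

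**The concern.** Patients on the same course share an educator, a timetable and deliberate discussion with one another, so a shared course effect on HbA1c is a plausible result of the design. It would arise in one arm only. The variance of the FLASH mean would then exceed what a patient-level ANOVA reports, and the error would lie on the anti-conservative side of the primary comparison. The Discussion section links a beneficial result to certification of the programme in Germany, so the false-positive rate matters.

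This goes beyond detail left to an unseen analysis plan. The article fixes a number of patients and names a model, and both rest on independence. A later plan could add a model term, but the stated 86 and 0.8 would still contain no allowance for it.

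**Working it through.** **Inputs from the protocol.** Difference 0.3 and SD 0.7 percentage points, alpha 0.05, power 0.8, 86 evaluable per arm, 20% non-evaluable (Sample size calculation); course size 3 to 8 (content of FLASH).

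**Assumptions.** Two-sided test (it reproduces the stated figure; one-sided gives 68 per arm); total SD 0.7 in both arms; ICC 0.01 to 0.10 within course; no centre effect in the main table; normal approximation.

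**Step 1: the plan's own figure.** n = 2 × (1.960 + 0.842)² / (0.3/0.7)² = 85.5, rounded up to 86. Then 86/0.8 = 107.5, rounded up to 108 per arm and 216 in total. The stated numbers come out exactly, so no design effect is included. At 86 per arm, SE = 0.7 × √(2/86) = 0.1067, and power = Φ(0.3/0.1067 − 1.960) = Φ(0.850) = 80.2%.

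**Step 2: clustering in the FLASH arm only.** With m analysed patients per course:

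- Design effect in that arm: DE = 1 + (m − 1) × ICC
- True SE = 0.7 × √((DE + 1)/86)
- Ratio of true to reported SE: r = √((DE + 1)/2)
- ANOVA as written, type I error: 2 × (1 − Φ(1.960/r))
- ANOVA as written, rejection at the planned effect: Φ(0.850/r)
- Valid cluster-adjusted test, power: Φ(0.3/true SE − 1.960)

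**Step 3: one case in full.** ICC 0.05 and m = 5.5, the midpoint of 3 and 8: DE = 1 + 4.5 × 0.05 = 1.225; true SE = 0.7 × √(2.225/86) = 0.1126; r = √(2.225/2) = 1.055. Type I error = 2 × (1 − Φ(1.858)) = 6.3%. Rejection by the ANOVA = Φ(0.806) = 79.0%. Valid-test power = Φ(2.664 − 1.960) = Φ(0.704) = 75.9%.

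**Step 4: the range.**

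| ICC | m | DE | r | ANOVA: type I error | ANOVA: rejection at planned effect | Valid test: power |
|---|---|---|---|---|---|---|
| 0.01 | 3 | 1.02 | 1.005 | 5.1% | 80.1% | 79.9% |
| 0.01 | 5.5 | 1.045 | 1.011 | 5.3% | 80.0% | 79.4% |
| 0.01 | 8 | 1.07 | 1.017 | 5.4% | 79.8% | 78.9% |
| 0.05 | 3 | 1.10 | 1.025 | 5.6% | 79.7% | 78.3% |
| 0.05 | 5.5 | 1.225 | 1.055 | 6.3% | 79.0% | 75.9% |
| 0.05 | 8 | 1.35 | 1.084 | 7.1% | 78.4% | 73.7% |
| 0.10 | 3 | 1.20 | 1.049 | 6.2% | 79.1% | 76.4% |
| 0.10 | 5.5 | 1.45 | 1.107 | 7.7% | 77.9% | 71.9% |
| 0.10 | 8 | 1.70 | 1.162 | 9.2% | 76.8% | 67.7% |

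The last column belongs to a different analysis from the two before it. With Satterthwaite degrees of freedom it falls by a further 1 to 4 points, for example from 75.9% to 74.1% at ICC 0.05 and m = 5.5.

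**Step 5: if whole centres were randomised.** Both arms would be clustered. With 172/40 = 4.3 evaluable patients per centre, DE = 1 + 3.3 × ICC and SE = 0.7 × √(2 × DE/86). Power of a valid test is 79.0%, 74.0% and 68.3% at ICC 0.01, 0.05 and 0.10; type I error of the ANOVA as written is 5.4%, 6.9% and 8.9%.

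**The case against.** A reader might infer that the trial has both about 73% power and an inflated type I error, and that the stated 80% is simply not delivered. The document supports neither. The low power figures belong to a cluster-adjusted test, which holds its level; the inflated type I error belongs to the unadjusted ANOVA, which loses 0 to 3 points at the planned effect. Both depend on an ICC that the document does not give. At 0.01 the effect is trivial, and delivery is standardised by 8 hours of instructor training, a written curriculum and site visits, which should limit variation between educators.

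Courses may also be small. With 108 FLASH patients over 40 invited centres, the average is 108/40 = 2.7 per centre, which points to the low rows of the table. Against that, 40 is the number invited, and 2.7 is below the minimum course size of three, so not every centre could run a course at even recruitment. With 20% non-evaluable, a course of 8 leaves 8 × 0.8 = 6.4 analysed: at ICC 0.10 this gives 70.3% power or 8.2% type I error, so the last row is an extreme case.

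If all 108 per arm entered the intention-to-treat analysis by carrying the last observation forward, a valid test with 5 per course would have 82% to 88% power over the assumed ICC range. That requires that imputation does not dilute the effect, and it does not repair the type I error.

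Finally, controls are not free of clustering: both arms attend the same kind of practice, whose physicians stay responsible for therapy. If patients are randomised within centres, ignoring the centre makes the ANOVA conservative and partly offsets the course effect. With 4 per arm per centre and course ICC 0.05, the variance factor is 1.15 + 1 = 2.15 against 2, giving 5.9% type I error. If a further 0.05 of the variance lies between centres, it cancels from the difference and the factor falls to 2.05, giving 5.3%. This stands, and it is why the remedy must include centre.

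**Conclusion.** The concern holds as a conditional one. The documents establish group delivery in one arm, a sample size with no allowance for it, and a named model with no course term. For any positive course correlation not offset by centre effects, the ANOVA as written reports standard errors that are too small. Over the assumed ranges its true type I error is about 5.1% to 9.2%, with rejection at the planned effect at about 77% to 80%. A valid test on 86 per arm has about 79% to 80% power at ICC 0.01, 74% to 78% at 0.05 and 68% to 76% at 0.10, so the stated 0.8 holds only if the course ICC is near zero. The document cannot say which row of the table applies; small courses and within-centre allocation would put the trial towards the milder end.

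**What to change.** - **Model.** Analyse the primary HbA1c endpoint with a partially nested mixed model: a random course effect in the FLASH arm, a centre effect in both arms, and small-sample degrees of freedom. It needs the course identifier, which the centres know. The case report form is not shown, so whether it is already recorded cannot be judged; if not, it should be.
- **Randomisation.** State in Recruitment and randomisation whether patients are allocated within centres or whole centres are allocated. If centres are, cluster both arms by centre; a model that treats each control as an independent unit would then be wrong.
- **Power statement.** In Sample size calculation, make the 0.8 conditional on an assumed ICC and an analysed course size, and show a range such as the one above in place of a single figure.

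Cost: one or two model terms, one identifier and a slightly less favourable stated power. No extra patients and no change to the programme.
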